### Equipment

The ICU-CARE CPET protocol will be performed using an upright cycle ergometer (Lode Corival | CPET, Lode BV Medical Technology). The pulmonary oxygen uptake ($\dot{V}O_{2}$), carbon dioxide production ($\dot{V}{CO}_{2}$), and the respiratory exchange ratio of $\dot{V}{CO}_{2}$/$\dot{V}O_{2}$ will be collected, monitored, and reported mid-5 of 7 breaths averaged using the Ultima CardiO2 gas exchange analysis system metabolic cart (MGC Diagnostics). A fitted air-cushioned face mask (preVent) and a bidirectional breath-by-breath volume sensor (preVent) will be used to collect the ventilatory variables. The Ultima CardiO2 will be calibrated before each test by using automated gas and flow calibrations as well as quality assurance to ensure compliance with the procedures recommended by the ATS/ERS pulmonary function acceptability and repeatability guidelines, as described in the user manual. Heart rate will be recorded using a 12-lead Mortara electrocardiogram (ECG) embedded in the Ultima CardiO2 system [48]. Blood pressure will be recorded every 2 minutes using the Tango M2 Stress Test Monitor (SunTech Medical) system during the exercise test.

NIRS is a noninvasive optical technology that provides information on microvascular oxygen delivery and local tissue utilization in skeletal muscle during exercise [49,50]. This technology provides insight into the concentration and oxygenation of biological tissues through the status of light-absorbing chromophores, such as hemoglobin (Hb) and myoglobin (Mb) within the near-infrared region (700‐900 nm) penetrating several millimeters [25]. The NIRS device (PortaMon, Artinis Inc) will be placed on the vastus lateralis muscle [51-53], about 12‐14 cm above the knee, secured by a band to minimize motion artifacts during cycling exercise. Adipose tissue thickness will be measured over the vastus lateralis site using Sonosite PX Ultrasound System (FUJIFILM Sonosite, Inc).

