#### Constant Work Rate Phase (On-Kinetics)

The CWR phase will entail a 5-minute steady-state moderate-intensity upright cycling exercise at the desired intensity of 30%, relative to the individual’s estimated $\dot{V}O_{2reserve}$ (as described below in the .$\overset{˙}{\;V}O_{2reserve}$Calculation section) to perform exercise, with a cadence of 60 rpm [28]. In a recent publication, our team used a 4-step process to standardize and determine the optimal CWR exercise intensity during a CPET protocol [28]. We will adopt and adapt these steps to derive a CWR intensity for ICU survivors, as outlined below.

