### Data Analysis

Similar to the $\dot{V}O_{2}$ analysis conducted on healthy adult populations [28], $\dot{V}O_{2}$ on-kinetics (rest-to-exercise transition), $\dot{V}O_{2peak}$, and $\dot{V}O_{2}$ off-kinetics (exercise-to-recovery transition) will be analyzed in the ICU-CARE CPET within a single bout—reporting the measured and predicted $\dot{V}O_{2peak}$ (mL kg^−1^ min^−1^), measured SS $\dot{V}O_{2}$ at CWR (mL kg^−1^ min^−1^), “actual” calculated 30% $\dot{V}O_{2reserve}$ (mL kg^−1^ min^−1^), and targeted intensity achieved at CWR as a percentage (%). Additionally, NIRS will be analyzed to evaluate skeletal muscle microvascular oxygenation. The primary variables will be pulmonary $\dot{V}O_{2}$, deoxyhemoglobin (HHb; deoxy[Hb+ Mb]), and TSI ($\frac{\left[oxy\left(Hb+Mb\right)\right]}{\left[oxy\left(Hb+Mb\right)\right]+\left[deoxy\left(Hb+Mb\right)\right]}*100$), measured noninvasively at a sample rate of 10 Hz.

Skeletal muscle oxygenation measured by NIRS (Portamon, Artinis Medical Systems) will be transmitted wirelessly into OxySoft software, time-synched with the metabolic cart with real-time impulse by inserting key commands on the NIRS computer (listed in Figure 1). On OxySoft, export NIRS data to Microsoft Excel, then adjust to timestamps as described above and illustrated in Figure 2. For a combined analysis, $\dot{V}O_{2}$ and NIRS data will be preprocessed using a customized LabVIEW code (LabView v20.0.01, National Instruments Corp), specifically designed to perform the required analyses. The first analysis removes noise and motion artifacts. Initially, outliers will be removed by applying 2 standard deviations in a window size of 7 seconds, then applying a 350-second moving average, linearly interpolated to provide second-by-second values [52]. Then, the data is resampled at 1 Hz and time-aligned with each transition to be synchronized with the metabolic cart.

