With exercise starting at zero, subsequent analysis will be performed using a mono-exponential model to fit the pulmonary or primary component of the $\dot{V}O_{2}$ response (ie, phase II) by skipping the cardiogenic phase (ie, phase I), as previously recommended [33,58], left-shifting at 20 s in length [52]. Then, the steady-state $\dot{V}O_{2}$ (SS $\dot{V}O_{2}$ or phase III) will be calculated as the average of the last 2 minutes of the CWR exercise phase [28]. The mono-exponential fitting is characterized by $\dot{V}O_{2}$ parameters, including tau (τ), time delay (TD), amplitude A_0_ and A_1_, and mean response time (MRT), where τ is defined as the time constant of the exponential function, representing the time taken to reach 63% of the steady-state or final value; TD records the delay to the exponential response start (ie, phase II) (the model is not constrained to pass through the origin) before oxygen uptake responds to exercise; A_0_ represents the baseline value (resting $\dot{V}O_{2}$), whereas A_1_ represents the change of amplitude from baseline to steady-state $\dot{V}O_{2}$ (ie, SS $\dot{V}O_{2}$ – baseline value); and MRT, defined as TD + τ, representing the overall time to adjust the rate of $\dot{V}O_{2}$ to changes in workload [28]. At the end of the incremental phase, $\dot{V}O_{2peak}$ will be defined as the highest value of the last 30 seconds before volitional exhaustion after applying a 20-second moving average [59,60]. The quality of the fitting will follow our previous protocol [28]. The analysis of residuals, the degree of linear correlation between the experimental data and fitted function (*r*), the 95% CI band, and the significance level (*P* value) of the estimated parameters are used to determine the quality of the fitting.

The HHb signal will be normalized using a 60-second average before the exercise begins, then analyzed by detecting the nadir, occurring after a sudden decrease in HHb signal, to exclude data not associated with muscular $\dot{V}O_{2}$ dynamics, referring to the muscle pump [61]. After the nadir, HHb increases monoexponentially, representing the $\dot{V}O_{2}$ dynamics during the onset of exercise [27,62-64].

The HHb monoexponential function is expressed in the equation below:

$$HHb\;{\left(t\right)}^{\;}=HHb_{bl}+a\left[1-e^{-\left(t-TD\right)/\tau }\right]$$

where HHb_bl_=HHb baseline, *a*=amplitude, *e*=mathematical constant, *t*=time, TD=time delay, and τ=time constant.

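### VO2 kinetics fits are judged by r, CI bands and P values from smoothed, 1 Hz interpolated data, which makes imprecise fits look precise

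*Protocol article*

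**What the plan says.** All references are to the protocol article.

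- **Equipment:** gas exchange is "reported mid-5 of 7 breaths averaged" at the metabolic cart.
- **Data Analysis, preprocessing:** the cart's VO2 and the "NIRS data will be preprocessed using a customized LabVIEW code". Outlier handling is the first step: "outliers will be removed by applying 2 standard deviations in a window size of 7 seconds". The smoothing and interpolation step is worded as "then applying a 350-second moving average, linearly interpolated to provide second-by-second values". The last step before fitting reads: "Then, the data is resampled at 1 Hz and time-aligned with each transition".
- **Constant Work Rate Phase (On-Kinetics):** "The CWR phase will entail a 5-minute steady-state moderate-intensity upright cycling exercise". There is one such transition per session.
- **Data Analysis, fit:** a mono-exponential is fitted after the first 20 s are skipped. Fit quality is judged by analysis of residuals, by r between data and fitted curve, by the 95% CI band, and by the P value "of the estimated parameters are used to determine the quality of the fitting". The section also says that fit quality follows the team's earlier study in healthy adults.
- **Evaluation of Exercise Capacity in ICU Survivors:** residuals, r and P value are named again.

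Neither section gives a cut-off for any criterion, or mentions autocorrelation or effective sample size.

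**The concern.** VO2 is measured once per breath. Overlapping seven-breath averages and linear interpolation add rows to the data set but no information. A least-squares routine that counts each second as an independent observation divides a shrunken residual variance by an inflated number of points. The standard errors of tau, time delay and amplitude become too small, the P values too small and r too high. Three of the four listed criteria are therefore distorted in the favourable direction.

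This matters because suitability for quantitative measurement of kinetics is part of the second hypothesis (Introduction). The protocol also expects to describe heterogeneity between patients and individual recovery trajectories (Evaluation of Exercise Capacity in ICU Survivors). Both need an honest statement of how well each person's tau is known. If precision is overstated, estimation noise can be read as physiological difference between patients.

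**Working it through.** **No stated figure.** The protocol gives no interval width or acceptance rate, so there is nothing to reproduce. The check asks how far the nominal interval for tau departs from its true sampling error.

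**Inputs from the document:** mid-5-of-7 averaging (taken as the mean of seven breaths without the highest and lowest), interpolation to 1 s, one 5-minute transition, first 20 s skipped, mono-exponential fit.

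**Assumptions, not in the document:** independent breath noise, its SD, the VO2 amplitude, breathing rate and tau. The fit window was 20 s to 290 s. The 2-SD outlier step was not simulated. The 350-second average was left out of the main comparison, so the result does not depend on it.

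**Is the assumed amplitude reasonable?** The target rise is 0.30 × (Equation 1 − resting VO2). For two illustrative participants:
- Male, 60 y, 175 cm, 80 kg: Equation 1 gives 2.339 × 0.75 = 1.754 L/min; rest is 3.5 × 80 = 0.280 L/min; rise = 0.30 × 1.474 = 0.44 L/min.
- Female, 60 y, 162 cm, 70 kg: 1.534 × 0.75 = 1.150 L/min; rest 0.245 L/min; rise = 0.30 × 0.905 = 0.27 L/min.

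An amplitude near 0.3 L/min is thus typical of the on-transition, and 1.0 L/min is generous.

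**Points against information.** From 20 s to 290 s is 4.5 min. At 15-25 breaths/min this gives about 67-112 breaths, but 271 one-second points.

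**One setting in detail** (amplitude 0.30 L/min, noise SD 0.08 L/min, 22 breaths/min, tau 45 s, 250 runs). The actual SD of fitted tau is about 14-15 s.

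| Data fitted | Reported SE of tau | r |
|---|---|---|
| Raw breaths | 12.3 s | 0.63 |
| 1 Hz interpolation | 5.9 s | 0.71 |
| Mid-5-of-7, then 1 Hz | 2.5 s | 0.92 |

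The drop can be checked by hand. Linear interpolation leaves on average 2/3 of the noise variance (the mean of u² + (1−u)² over 0 to 1). The count goes from 22 × 4.5 = 99 to 271. The expected SE ratio is √(2/3 × 99/271) = 0.49, and 12.3 × 0.49 = 6.1 s, close to 5.9 s. If the true standard error is taken as 12.3 s, coverage is 2Φ(1.96 × 5.9/12.3) − 1 = 65% after interpolation, and 2Φ(1.96 × 2.5/12.3) − 1 = 31% after mid-5-of-7 plus 1 Hz.

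**Coverage of the nominal 95% CI for tau:**

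| Assumptions | Raw breaths | 1 Hz | Mid-5-of-7 + 1 Hz |
|---|---|---|---|
| SD 0.04-0.08, amplitude 0.3-1.0, 16-25 breaths/min | 92-96% | 59-70% | 30-35% |
| SD 0.04-0.12, amplitude 0.35, 15 or 25 breaths/min, tau 30 or 60 s | 86-96% | 56-77% | 24-39% |

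In the second set the reported SE after mid-5-of-7 plus 1 Hz is about 4 to 7 times too small (for example 0.80 s against an actual spread of 4.4 s). Residual lag-1 correlation is 0.97-0.99.

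**A poor-signal case** (amplitude 0.10 L/min, SD 0.12 L/min, 20 breaths/min, tau 45 s). The actual spread of tau is about 40 s. Tau has P<.05 in 3% of raw fits and 79% of processed fits.

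**The case against.** The strongest reply has five parts.

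1. **Residuals are the first criterion listed.** A reader might infer that r, the CI band and P are the only guard against an unusable fit. The text does not support that: residual analysis is named in two sections. This stands. However, no rule for it is given, and the processing itself makes the residuals of a correct model strongly autocorrelated, which weakens them as a sign of misfit.
2. **No cut-off is stated.** A reader might infer that nearly every fit will be accepted. Without thresholds no pass rate can be computed, so the supportable statement is that imprecise fits can look acceptable. This stands.
3. **The procedure is deferred to an earlier study that is not shown, and the preprocessing code is custom-written.** A correction for autocorrelation cannot be excluded. The article restates the criteria without one, so the finding is conditional on ordinary least-squares intervals.
4. **The written smoothing is a 350-second average, which was left out of the main comparison.** That window exceeds the 300-second work phase and causes bias: taken literally, a true tau of 30 s is fitted as about 215-235 s. It is a separate problem. The present one remains whether or not that figure is literal.
5. **Little rests on individual standard errors.** The primary outcome is feasibility, the sample size rests on VO2peak agreement, and cohort results are means with SD or CI. This stands and limits the weight of the point.

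The simulated work-phase settings model an on-transition. The off-transition and the HHb signal were not modelled separately.

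**Conclusion.** The point holds as a defect in a stated analysis choice. If the intervals and P values are ordinary least-squares quantities, the nominal 95% CI for tau covers roughly 59-70% after 1 Hz interpolation and 30-35% once mid-5-of-7 averaging is included, against 92-96% on raw breaths. The size depends on assumed noise, amplitude and breathing rate; the direction was the same in every setting tried. Raw-breath intervals are not perfect either: coverage fell to 86% in the wider set and to about 80% in the noise-dominated case.

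The consequence is limited to individual kinetics precision, which bears on the second hypothesis and the heterogeneity aims. The primary feasibility outcome and the sample size of 48 are not touched. It should be changed before kinetics are analysed, but it does not threaten the study.

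**What to change.** - Fit the exponential to breath-by-breath VO2 with outlier breaths removed, without mid-5-of-7 averaging, moving average or interpolation. Confirm that the cart can export unaveraged breaths.
- Keep the 1 Hz series for display and for alignment with NIRS.
- Report the CI for tau from the breath-level fit. If a 1 Hz series must be fitted, use one without the long moving average and take the interval from a block bootstrap of residuals. A bootstrap would not remove bias from a 350-second window.
- Judge precision by the width of that interval against a limit fixed before analysis, not by r or P. State what residual pattern counts as misfit.

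The cost is a change in analysis code and one paragraph of text. Reported intervals will be wider, and some participants' kinetics will be declared too imprecise to interpret individually. No test procedure changes.

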### Missing Data

Missing data, if any, will be reported with an explanation upon publication.

## Results

### Outcome Measures

Our primary methodological outcome for this study will be the feasibility of recruitment and completion of the protocol. The secondary outcome will be validation of a priori physiological equations through assessment of agreement between predicted and measured variables of $\dot{V}O_{2peak}$ and $\dot{V}O_{2CWR}$. Physiological observations of exercise capacity and skeletal muscle oxygenation derived from the protocol will also be considered secondary outcomes.

### Anticipated Feasibility of Participation and Study Protocol Completion

Recruitment is anticipated to begin in June 2026 and is expected to be completed in 2029/2030. Two patients have participated in a prior pilot version of the protocol in 2025, which involved testing the phases of the exercise protocol with commercial population-based equations and application of the NIRS during exercise. This was done to determine equipment functionality, data quality, transition between CPET phases, and sample values of $\dot{V}O_{2peak}$ in the ICU population; results from these pilot participants will not be used in the main study. Based on this pilot, we have incorporated a contemporary standardized population-based equation for estimation of $\dot{V}O_{2peak}$ (Equation 1). The protocol registry has been amended to align with the primary and secondary outcomes listed herein, and the removal of unrelated outcomes and analyses from prior study iterations.

We expect to screen 1‐2 patients per week in the ICU, based on our local ICU data of approximately 1350 admissions per year, 68% bed utilization of mechanical ventilation, and a median duration of mechanical ventilation of 5.8 days. Of the screened patients, we aim for 50% enrollment to participate in follow-up via telephone after ICU discharge. Based on prior studies evaluating ICU-AW [45], we expect a significant loss to follow-up and/or inability to return to the clinic for the study. We are targeting a feasibility of enrollment rate of 1 participant per month throughout the study duration to generate preliminary outcome measurements to inform future studies. Of the individuals who are participating, our protocol feasibility metric will be ≥80% completion of all phases of the ICU-CARE CPET, enabling integrated evaluation of $\dot{V}O_{2peak}$, $\dot{V}O_{2}$ on/off kinetics, and local microvascular oxygenation to provide quantitative evaluation of exercise capacity and health outcomes in the ICU survivor population.

### Validation of ICU-Specific Protocol Adaptations

We will determine whether our ICU correction factor of 0.75 is an acceptable method for estimating $\overset{˙}{V}O_{2peak}$ from population equations. The statistical analysis for comparisons between predicted versus measured variables—specifically $\dot{V}O_{2peak}$ and $\dot{V}O_{2CWR}$—will be performed with (1) percentage differences between predicted and measured variables for general weighted inspection of the difference, (2) linear regression/correlational analysis with measured variables as the dependent and predicted as the independent variable, (3) Bland-Altman analysis [65] to assess the agreement between predicted and measured variables, and (4) Cohen *d* test to assess the size of the difference/similarity between predicted and measured variables; the difference between measured and predicted values will be considered clinically significant (ie, discordant) if they exceed a Cohen *d* value of 0.5. The statistical significance level will be set at *P*<.05.

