Research suggests that 1 of 3 ICU survivors experience reduced $\dot{V}O_{2peak}$ [21], often falling below 80%‐85% of predicted values [5,21,22] during the first year after ICU discharge. Based on these studies, we have decided to use a correction factor of 0.75 (75%) to account for the reduced $\dot{V}O_{2peak}$ in the ICU survivor population. This is incorporated into Equation 1 (in step 1) and will be evaluated during this study. We have also adapted the incremental phase of this protocol (W) based on patients’ self-reported functional status (5, 10, 15, or 20 W min^−1^), derived from a practical guide for CPET [56], suggesting the use of the staircase question to inform ramp modifications. Research suggests a linear relationship shared between the number of steps climbed, minute ventilation, and $\dot{V}O_{2peak}$ [68]. Our practical staircase question [56] will be compared with the mMRC using a correlational analysis within the prospective study, offering a tailored approach to promote inclusion. In future studies, analysis of the statistical significance correlation between mMRC and staircase question steps can be conducted to assess its relationship, depending on sample size, to get a significant result, to validate the staircase question to be used instead of the mMRC scale, or in conjunction.

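### The only numeric criterion for judging the 0.75 correction factor is Cohen d above 0.5, which measures standardized mean bias and not individual agreement; no absolute limit of agreement is set

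*Protocol article*

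**What the plan says.** For VO2peak, the section on validation of ICU-specific protocol adaptations states its purpose as a decision ("We will determine whether our ICU correction factor of 0.75 is an acceptable method for estimating" this quantity). It lists four analyses, for both VO2peak and VO2 at the constant work rate (CWR):

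- percentage differences, meant for inspection;
- a regression of the measured on the predicted values, with correlation;
- "Bland-Altman analysis [65] to assess the agreement between predicted and measured variables";
- Cohen d, under which a difference "will be considered clinically significant (ie, discordant) if they exceed a Cohen" d of 0.5.

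The section sets a significance level of P<.05 but does not say which test it applies to or how it bears on acceptability. Neither the percentage differences nor the Bland-Altman limits have an acceptance limit. The SD that forms the denominator of d is not stated.

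The section on statistical analysis and sample size bases N = 48 on Bland-Altman agreement for VO2peak. It defines delta as the largest acceptable agreement limit, but gives it only as delta/sigma = 2.9, and says that sigma will be known only once the study is complete.

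**The concern.** Whether a prediction equation is acceptable depends on how far predictions miss in individual people. Here that has a direct consequence. Equation 1 gives the predicted VO2peak, Equation 2 turns it into a target VO2, and Equation 3 turns that into the watts that the participant cycles against. A small average error does not show that individuals were given the intended relative intensity.

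Cohen d summarizes only the average error, rescaled by an SD. Two sets of predictions with the same d can have very different individual errors. If the SD is that of the differences, a noisier predictor is allowed a larger bias before it is called discordant. Delta is also expressed only in units of sigma, so no error in mL/kg/min or % is declared unacceptable anywhere in the article. The conclusion about 0.75 could then follow the one threshold that is stated, while wide limits of agreement are reported beside it with nothing to judge them against.

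**Working it through.** **Inputs from the article.** n = 48; d threshold 0.5; delta/sigma = 2.9; mu/sigma = 0.2; alpha 0.05 (taken as two-sided); power 80%; Equation 1 with the factor 0.75.

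**Assumptions, not in the article.** Biases of 2 and 3 mL/kg/min; SDs of differences from 2 to 8; the example participants; Equation 1 read as litres per minute.

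**1. The plan's own figure.** Require the two-sided 95% confidence bounds of both limits (mean ± 1.96 SD) to lie within ±delta. The standard error of a limit is sigma × sqrt(1/n + 1.96²/(2(n−1))). With power from the noncentral t distribution, 80% is first reached at n = 46 (80.7%), and n = 48 gives 82.5%. Direct simulation at n = 48 gives 80.4%. The planned 48 reproduces, so the sample size is not at fault.

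**2. d with the SD of differences.** d = |bias|/SD, so the tolerated bias is 0.5 × SD. Limits of agreement are bias ± 1.96 SD (mL/kg/min).

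| Bias | SD | d | Label | Limits of agreement |
|---|---|---|---|---|
| 2 | 2 | 1.00 | discordant | −1.9 to 5.9 |
| 2 | 5 | 0.40 | not discordant | −7.8 to 11.8 |
| 3 | 4 | 0.75 | discordant | −4.8 to 10.8 |
| 3 | 8 | 0.38 | not discordant | −12.7 to 18.7 |

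At a given bias, the more precise predictor fails and the less precise one passes.

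**3. Scale.** For a man of 60 years, 175 cm and 85 kg, Equation 1 gives (2.2585 + 0.6197 + 0.5642 − 0.9913 − 0.0761) × 0.75 = 1.781 L/min. Divided by 85 kg, that is 21.0 mL/kg/min. For a woman of 60 years, 162 cm and 70 kg, it gives (2.0907 + 0.5104 − 0.9913 − 0.0761) × 0.75 = 1.150 L/min, or 16.4 mL/kg/min. The upper limit of 11.8 in the second row is then 56% (11.8/21.0) to 72% (11.8/16.4) of the predicted value, with d = 0.40.

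**4. d with a pooled SD.** Assume SDs of 4 (predicted) and 6 (measured). The pooled SD is sqrt((16 + 36)/2) = 5.10, so the tolerated bias is 2.55 whatever the correlation. The SD of differences is sqrt(16 + 36 − 48r). The half-width of the limits is 5.8 at r = 0.9 and 14.1 at r = 0. Here scatter from poor correlation does not lower d, but d does not register it either.

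**5. Sampling error at n = 48.** For a paired d of 0.5, the 95% half-width is 1.96 × sqrt(1/48 + 0.25/96) = 0.30. With a true paired d of 0.6, the chance that the sample value is 0.5 or less is 25% (noncentral t, 47 df). With a pooled SD and equal SDs, simulation gives 31% at r = 0, 25% at r = 0.5 and about 10% at r = 0.9.

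**6. What a purely standardized delta does.** At n = 48 the confidence half-width of a limit is 2.01 × 0.248 = 0.50 SD. If delta were read as 2.9 times the observed SD, the condition |d| + 1.96 + 0.50 ≤ 2.9 reduces to |d| ≤ 0.44. The Bland-Altman criterion would then be another cut-off on d, with the same blindness to absolute error.

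**The case against.** The article does not say that d alone decides. It lists four analyses, and the d sentence labels a difference as discordant. It does not say that d of 0.5 or less makes the factor acceptable or overrides the Bland-Altman limits. Wide limits would appear in the report. This stands, and it rules out the reading that large individual errors would be hidden or that d is the declared sole test. What remains is that no other analysis has a limit that could count against a low d.

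A reader might also infer that nothing planned informs the value of the factor. That is not supported. Percentage differences imply it: if measured values averaged 8% above predicted, the implied factor would be 0.75 × 1.08 = 0.81. The correlation coefficient is the same for any constant factor, but the regression slope is not; it scales as 1/factor.

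That d rewards imprecision is exact only when the denominator is the SD of differences, which the article does not state. The SDs and biases above are illustrations, and SD 8 is extreme against predicted values of about 16 to 21.

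A reader might further infer that the basis for 0.75 is contradictory, since one section cites an average 25% reduction and the discussion says "Research suggests that 1 of 3 ICU survivors experience reduced" VO2peak, often below 80% to 85% of predicted. These are different quantities. Values often below 80% to 85% are compatible with an average of 75%, and how the one-in-three figure fits cannot be settled without the cited studies.

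Finally, an unseen analysis plan may hold an absolute delta. That is possible, but the article itself states a decision threshold, and that threshold does not suit the question.

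**Conclusion.** The point holds in this form: the only numeric criterion stated for judging the 0.75 factor is Cohen d above 0.5. It measures standardized mean bias, is blind to individual error under either denominator, and with the SD of differences tolerates more bias as scatter grows. As a point-estimate rule at n = 48, it passes a true paired d of 0.6 about one time in four. The direction of these effects does not depend on the assumed SDs and biases; their size does.

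Severity is should-fix. Agreement is a secondary outcome, feasibility is primary, and the results are meant to inform later studies. The sample size of 48 reproduces and is not in question.

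**What to change.** - Keep Cohen d as description only, and state its denominator.
- Before any data are seen, fix delta in mL/kg/min or % with a stated rationale. Call the factor acceptable only if the 95% confidence bounds of both Bland-Altman limits lie within ±delta. This matches the sample-size method already used. Say whether VO2 at the CWR is judged the same way, with its own limit, or only described.
- Add an estimate of the factor: the mean or geometric mean ratio of measured to uncorrected predicted VO2peak with its 95% CI, and report whether 0.75 lies inside. This addresses average calibration only, so it supplements the limits-of-agreement criterion and does not replace it.

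**Cost.** Wording and one more analysis of data already planned. The conclusion may be less favourable. The power statement also becomes conditional: at mu/sigma = 0.2, N = 48 gives about 80% power only if sigma ≤ delta/2.9. For illustrative deltas of 3.5, 5 and 7 mL/kg/min, sigma must be at most 1.2, 1.7 and 2.4. The article should say so, since sigma is unknown. Setting delta after sigma has been observed would lose most of its value.
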